#### Control group (CG)

2.5.2

Participants in the CG will not participate in supervised exercise sessions. They will only be informed at the beginning of the study that performing 30 minutes of moderate-intensity physical activity several days a week is associated with health benefits. During the study, participants in this group will be contacted monthly by phone to provide general support and counseling without discussing exercise or physical activity.

### Outcomes

2.6

#### Primary outcomes

2.6.1

##### Saccharin transport time

2.6.1.1

It is a nasal technique for to measure mucociliary clearance, widely reported as a simple, non-invasive, valid and reproducible method.^[23]^ The nasal cavity has a respiratory epithelium similar to the rest of the respiratory tract, and nasal mucociliary transport has a good correlation with tracheobronchial transport.^[24]^ Subjects will be seated and positioned with 10 degrees of neck extension. Granulated sodium saccharin (250 μg) will be placed 2 cm inside the right nostril under visual control. The time from particle placement until the first perception of a sweet taste in the mouth will be recorded in minutes by a digital chronometer.

##### Secretion analysis

2.6.1.2

Mucus samples will be collected by voluntary coughing and expectoration into a glass. The mucus will be separated from the saliva and then evaluated in terms of its adhesiveness and purulence. After this initial evaluation, the respiratory secretions will be placed in plastic tubes and covered with mineral oil to prevent dehydration, followed by freezing for subsequent analysis.^[25]^ The evaluated parameters will be the surface properties, appearance, relative transport velocity on a frog palate, transport measured in a simulated cough machine, and the contact angle.^[26]^

##### Nasal lavage fluid

2.6.1.3

In a sitting position, participants will be instructed to tilt the head back at a 45° angle and close the nasopharynx with the soft palate. Five milliliters of 0.9% saline solution at room temperature will be instilled into each nostril, and subjects will be instructed to hold their breath without swallowing for 10 seconds. After 10 seconds, the individuals will blow their nose hard into a sterile plastic tube. The samples will be centrifuged (10 minutes, 5 °C), and the supernatant will be separated from the pellet and immediately transferred to sterile polypropylene tubes. The tubes will be coded and stored at −80 °C for determination of the cytokine levels.^[27]^

##### Exhaled breath condensate collection and pH analysis

2.6.1.4

It is difficult to obtain specimens noninvasively from the lower airways to assess inflammation. However, the exhaled breath condensate provides information about the lower to upper airways and can be performed repeatedly. The collection will be performed as described previously.^[28]^ The samples (2.0–2.5 mL) will immediately be divided into 500-μL aliquots and transferred to sterile polypropylene tubes, which will be encoded and stored for a maximum of four weeks at −80 °C for the determination of the cytokine levels. The pH of the samples will be measured immediately, and then the measured samples will be discarded.

##### Measurements of the nasal fractional exhaled nitric oxide

2.6.1.5

The nasal fractional exhaled nitric oxide level will be measure using a hand-held chemiluminescence analyzer (NIOX MINO Airway Inflammation Monitor, Aerocrine AB, Solna, Sweden). Three acceptable measures and mean values will be included in the analysis. The measurement range will be 5 to 400 ppb. The measurements will be performed according to a protocol defined by the American Thoracic Society.^[29]^

##### Cytokine analysis

2.6.1.6

The concentrations of tumor necrosis factor-alpha, interleukins 6 and 10 in nasal lavage fluid samples will be determined using high-sensitivity immunoassay (ELISA) performed according to the instructions of the supplier of the kit.

#### Secondary outcomes

2.6.2

##### Pulmonary function

2.6.2.1

Pulmonary function will be evaluated by Koko PFT System Spirometer (version 4.11, 2007 nSpire Health, Inc., Pulmonary Data Services). The forced expiratory volume in the first 2nd and forced vital capacity will be determined according to the guidelines from the American Thoracic Society/European Respiratory Society Task Force.^[30]^ The percentages of predicted spirometry values will be calculated from published Brazilian population data.^[31]^

##### Impulse oscillometry

2.6.2.2

Impulse oscillometry will be performed using a Jaeger IOS (Jaeger, Wurzburg, Germany).^[32,33]^ IOS parameters will be recorded, including respiratory impedance (Z), airway resistance at 5 Hz (R5), airway resistance at 20 Hz (R20), lung resistance at 5 Hz (X5), resonance frequency (Fres), and reactance area. It will enable analysis of the central and peripheral resistance of the respiratory system.

##### Respiratory muscle strength test

2.6.2.3

The respiratory muscle strength will be assessed using a previously calibrated digital manovacuometer (MVD 300, Globalmed, Porto Alegre, Brazil) with a variation of ±300 cm H_2_O. First, maximal inspiratory pressure will be measured from the residual volume, followed by maximal expiratory pressure from the total lung capacity. The test will be performed according to the Guidelines for Pulmonary Function Testing.^[31,34]^

##### Quality of life evaluation scale

2.6.2.4

The general health status of the patients will be assessed through the Medical Outcomes Study 36-Item Short-Form Health Survey.^[35]^ The quality of life in this group of patients will be evaluated using the Quality of Life in Bronchiectasis Questionnaire^[11]^ and the Leicester Cough Questionnaire to assess the physical, psychological, and social impacts of chronic cough.^[36]^

##### Analysis of heart rate variability

2.6.2.5

Heart rate variability will be assessed by spectral analysis using echocardiogram records.^[15]^ Participants will be placed in the supine position for 20 minutes on an electric orthostatic table. They will then be passively placed in a tilted position at 75° for another 20 minutes (tilt test). Electrocardiogram measurements (ML866 PowerLab, ADInstruments, Bela Vista, NSW, Australia) will be obtained in the lying and supine positions and during the tilt test. The respiratory rate will be set at 15 cycles per minute with the aid of a metronome.

#### Psychosocial measures

2.6.3

##### Minimental state examination

2.6.3.1

The minimental state examination is commonly used as a screening test for dementia.^[37]^ All volunteers will undergo this assessment to screen for cognitive losses that may compromise the answers to the quality-of-life questionnaires. The maximum score is 30. Scores less than 24 are used by some researchers and clinicians to indicate possible dementia.

##### Hospital anxiety and depression scale

2.6.3.2

The Hospital Anxiety and Depression Scale (HADS)^[38]^ is used to identify anxiety disorders and depression in physically ill patients. The HADS is divided into an anxiety subscale (Hospital Anxiety and Depression Scale-Anxiety Subscale) and a depression subscale (Hospital Anxiety and Depression Scale-Depression Subscale), both of which contain 7 interspersed items. The cut-off scores are 8 points for anxiety and 9 for depression.

### Sample size calculation

2.7

The sample calculation was performed based on the mucociliary clearance evaluated by the saccharine transport time.^[39]^ The detected effect should have an average of 4 minutes with a standard deviation of 3 minutes, alpha of 5%, and power of 95%. The results indicate that 60 volunteers would be needed with 15 in each subgroup.

### Statistical analysis

2.8

A biostatistician will analyze the data in a blinded manner. The normality of the data will be verified by the Shapiro–Wilk test. For comparing the values between 2 groups, the Student *t* test will be used for parametric variables and the Wilcoxon test will be used for nonparametric variables. Analysis of variance will be used for comparison between 3 or more groups, followed by a multiple comparisons test when indicated for parametric data or the Kruskal–Wallis test for nonparametric data. Data correlation will be assessed using the Pearson or Spearman correlation test for normal and nonnormal distributions, respectively. The level of significance will be set at 5%. Statistical analysis will be performed through the R version 3 (2013-05-16) (The R Foundation for Statistical Computing, Vienna, Austria) and SAS version 9.2 (Cary, NC).

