### Recruitment organization and randomization

2.3

The volunteers will be recruited in the pulmonology outpatient of Clinical Hospital of the Ribeirão Preto Medical School. A pulmonologist will evaluate HRCT results to determine eligibility. Only volunteers who satisfy all the criteria inclusion will be randomized using simple computerized randomization procedures. After, it will be divided into a pulmonary rehabilitation group and a control group (CG). These groups will be subdivided into a group that will be instructed to follow an exercise protocol and one that will not (Fig. 1). The allocation sequence will be generated by a researcher who is not involved in the assessment and interventions. After allocation to one of the groups, a blind examiner will conduct clinical evaluations and collect data to analyze the primary and secondary variables. Another evaluator will follow the exercise plan. All participants will be assessed at the start of the study after the 8th and 12th weeks. Volunteers may discontinue participation at any time if they wish. However, all efforts will be made to avoid missing data, mainly for the main target criteria, case a patient discontinues the trial, a final visit will be performed, and the data of this visit will be used for the calculation of the main criteria, the primary outcomes. The specific dealing of missing data will be determined in a data review meeting before starting statistical analyses.

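### A baseline is collected, but the tests named in section 2.8 state no use of it; adjusting for it would gain precision at almost no cost

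*Protocol article*

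**What the plan says.** Section 2.3 (Recruitment organization and randomization) sets three assessment times: "All participants will be assessed at the start of the study after the 8th and 12th weeks". Participants are "randomized using simple computerized randomization procedures", and no stratification is mentioned.

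Section 2.8 (Statistical analysis) uses Shapiro–Wilk to decide between parametric and nonparametric tests. "For comparing the values between 2 groups", these are Student's t test or the Wilcoxon test; for three or more groups they are ANOVA with multiple comparisons, or Kruskal–Wallis. Correlations are also planned. The section does not say which visit supplies the values or whether they are raw values or changes. It mentions no baseline covariate, within-person term or group-by-time term.

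Section 2.7 (Sample size calculation) rests on saccharin transport time: "The detected effect should have an average of 4 minutes with a standard deviation of 3 minutes", with 5% alpha and 95% power, concluding that "60 volunteers would be needed with 15 in each subgroup".

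**The concern.** The design is longitudinal, while the tests named are those of a single-occasion comparison between groups. The randomised comparison within bronchiectasis has about 15 people per arm, and simple randomisation does not guarantee even that split. At this size the arms can differ noticeably at baseline by chance. A comparison that ignores baseline carries part of that difference into the result, and its standard error is wider than it need be. At stake is precision, above all for effects smaller than the planned 4 minutes, for losses to follow-up, and for the outcomes on which the trial was not sized.

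**Working it through.** **Inputs.** From section 2.7: difference 4 min, SD 3 min, alpha 5%, power 95%, 15 per subgroup. Two-sided testing is an assumption, because the article does not state it. The baseline-to-follow-up correlation ρ is not given either; it is assumed here at 0.3, 0.5 and 0.7. The SD of 3 min is first taken as that of the raw value.

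**1. The plan's own figure.** n per group = 2 × [SD × (1.960 + 1.645) / difference]² = 2 × [3 × 3.605 / 4]² = 14.6, rounded up to 15; 4 × 15 = 60. This reproduces the article exactly. (One-sided, it would be 13 per group and 52 in total, which does not match.) The sample size is therefore that of a two-sample comparison with no baseline term. With the noncentral t distribution, power at 15 per arm is 94.1%.

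**2. Gain from ANCOVA.** Residual SD = 3 × √(1 − ρ²); SE of the arm difference = residual SD × √(2/15); power from the noncentral t with 27 degrees of freedom (28 unadjusted).

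| Analysis | Variance cut | Residual SD (min) | SE (min) | Power, 4 min | Power, 3 min |
|---|---|---|---|---|---|
| Unadjusted | – | 3.00 | 1.10 | 94% | 75% |
| ANCOVA, ρ = 0.3 | 9% | 2.86 | 1.05 | 96% | 79% |
| ANCOVA, ρ = 0.5 | 25% | 2.60 | 0.95 | 98% | 86% |
| ANCOVA, ρ = 0.7 | 49% | 2.14 | 0.78 | 99.8% | 96% |

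The 3-minute effect is illustrative and is not in the article. The ANCOVA rows are slightly optimistic, because they charge the degree of freedom but not the extra variance from whatever baseline imbalance occurs. For a normal covariate that is on average a factor 1 + 1/(28 − 2) = 27/26, about 4%. The net variance cuts are then 1 − 0.91 × 27/26 = 5.5%, 1 − 0.75 × 27/26 = 22% and 1 − 0.51 × 27/26 = 47%.

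**3. Chance imbalance.** If the baseline SD is also 3 min, the SE of the baseline difference is 3 × √(2/15) = 1.10 min, and the chance of a difference above 0.5 SD (1.5 min) is 17%. Only about ρ times the imbalance reaches the unadjusted result: 1.5 min becomes 0.45, 0.75 or 1.05 min at ρ = 0.3, 0.5 or 0.7. In simulation (100,000 runs, imbalance held at 0.5 SD) the type I error given that imbalance was 7.0% at ρ = 0.5 and 7.9% at ρ = 0.7. Averaged over all randomisations it is the nominal 5%.

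**4. A plain change score is not a safe substitute.** Its SD is 3 × √(2(1 − ρ)). At ρ = 0.3 this is 3.55 min, and power for 4 min falls to 84.6%. At ρ = 0.5 it equals the raw SD, and only above that does it help.

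**The case against.** The strongest reply is that this argues from silence in a condensed article. Section 2.8 does not call the t test unpaired, does not define the values compared, and does not say which Wilcoxon test is meant. A fuller analysis plan could supply change scores or covariates. The SD of 3 min might already be that of a change, in which case baseline is in use and the table above does not apply as it stands. The sample size and the named tests agree with each other, and at the planned effect the unadjusted test is adequately powered.

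Most of this stands, and it limits the point to a recommendation. It does not remove it: the article names specific tests, none of them as described uses the baseline, and a better analysis needs no new data. Even if the SD of 3 min is that of the change, ANCOVA still has the smaller variance, by the ratio (1 − ρ²) / [2(1 − ρ)] = (1 + ρ)/2, that is 0.65, 0.75 and 0.85 at ρ = 0.3, 0.5 and 0.7.

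Two stronger readings are tempting but not supported:

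- **Inflated type I error from repeated visits.** A reader might infer that ANOVA would treat visits as independent observations. The article applies ANOVA to groups, of which the design has four, and nowhere describes pooling weeks 8 and 12. If the visits were wrongly entered as independent ANOVA groups, positive within-person correlation would make the test of visits conservative: simulated rejection was 0.5% at a correlation of 0.5, against a nominal 5%.
- **A baseline biased by knowledge of the arm.** Section 2.3 says: "After allocation to one of the groups, a blind examiner will conduct clinical evaluations and collect data". A reader might infer that baseline is taken once participants know their arm. The sentence concerns examiner blinding. It does not say when participants learn their allocation, and the same section also places an assessment at the start of the study. This supports a request for clarification only.

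**Conclusion.** The point holds as a free improvement and not as an error that must be corrected. The unadjusted comparison is valid on average over randomisations and matches the sample size calculation. What it gives up is precision: nominally 9% to 49% of the variance for ρ between 0.3 and 0.7, a little less after the cost of estimating the adjustment. At the planned 4 minutes with 15 per arm the practical gain is small, from 94% to 96–99.8% power. It is worth more if the true effect is nearer 3 minutes, where power goes from 75% to 79–96%. These sizes rest on an assumed correlation, two-sided testing, the SD of 3 min being that of the raw value, and a full 15 per arm.

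**What to change.** In section 2.8, for saccharin transport time in the randomised bronchiectasis contrast, state that the primary analysis is the week-12 difference between arms with its 95% CI, from ANCOVA with the baseline value as covariate. An equivalent choice is a mixed model on weeks 8 and 12 with baseline, arm, visit and arm-by-visit, and participant as the repeated unit, reporting the week-12 contrast. Fix the analysis scale in advance (for example log minutes, with a rank-based sensitivity analysis) instead of letting Shapiro–Wilk choose the test. In section 2.3, clarify that baseline assessments are completed before allocation.

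The cost is one degree of freedom for the ANCOVA covariate and a few sentences of wording. No extra data or participants are needed, and the sample size can stay as it is.

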**Methods::**

Sixty subjects of both sexes between 18 and 60 years (30 volunteers with clinically stable bronchiectasis and 30 healthy volunteers) will be included. Participants with chronic obstructive pulmonary disease, decompensated cardiovascular or metabolic diseases, neuromuscular and musculoskeletal diseases, and active smokers will be excluded. Volunteers will be randomly allocated to the pulmonary rehabilitation or control groups. The primary outcomes will be nasal transport time as evaluated by nasal saccharin transport time, analysis of nasal lavage, enzyme immunoassay of exhaled expiration, and analysis of the mucus properties. The secondary outcomes will include pulmonary function tests, impulse oscillometry, heart rate variability analysis, and quality of life questionnaires.

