### Study participants and eligibility criteria

2.4

A total of 60 eligible participants with age between 18 and 60 years will be recruited. Of these participants, 30 will have been diagnosed with bronchiectasis that is not attributable to cystic fibrosis and confirmed by HRCT. These subjects will be clinically stable without any evidence of exacerbated bronchiectasis or changes in medical therapy in the previous 4 weeks.^[18]^ Participants will be excluded if they have a smoking history ≥10 pack years, diagnosis of chronic obstructive pulmonary disease,^[19]^ asthma,^[20]^ interstitial lung disease (clinical/radiological diagnosis), and medical conditions that can put the subjects at risk during the exercise protocol (eg, unstable cardiovascular disease) or conditions that may restrict the participant's ability to exercise (eg, severe orthopedic or neurologic impairments). The remaining participants will be 30 nonsmoker volunteers without lung disease and recruited from the community.

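### The exercise and control groups are defined inconsistently, and the analysis section does not fix exercise versus no exercise within bronchiectasis as the primary contrast

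*Protocol article*

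**What the plan says.** **Aim.** The abstract and the end of the Introduction give the question as the effect of exercise in patients with bronchiectasis.

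**Participants.** There are 60: 30 patients, and a second half described in section 2.4 as "The remaining participants will be 30 nonsmoker volunteers without lung disease and recruited from the community".

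**Groups.** Four places describe them.
- Abstract, Methods: "Volunteers will be randomly allocated to the pulmonary rehabilitation or control groups".
- Section 2.3, speaking of the control group (CG) and the rehabilitation group alike: "These groups will be subdivided into a group that will be instructed to follow an exercise protocol and one that will not".
- Section 2.5.1: the intervention group, without exception, receives the supervised programme twice a week for 12 weeks.
- Section 2.5.2: "Participants in the CG will not participate in supervised exercise sessions".

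**Sample size (section 2.7).** "The detected effect should have an average of 4 minutes with a standard deviation of 3 minutes", at 5% alpha and 95% power, leading to "60 volunteers would be needed with 15 in each subgroup".

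**Analysis (section 2.8).** Two groups are compared by Student's t test or the Wilcoxon test. For more groups: "Analysis of variance will be used for comparison between 3 or more groups, followed by a multiple comparisons test when indicated for parametric data", with Kruskal–Wallis as the nonparametric alternative. The section does not say which groups enter which test.

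**The concern.** The statements about the groups cannot all hold. If section 2.3 is taken literally, the CG contains exercisers and the rehabilitation group contains non-exercisers; sections 2.5.1 and 2.5.2 exclude both. The reading that fits 30 patients, 30 healthy volunteers and four subgroups of 15 is disease status crossed with exercise. Disease status can only be observed; exercise can be randomized.

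In that layout only two of the six pairwise comparisons are randomized exercise contrasts (within patients and within healthy volunteers). The other four compare patients with healthy people. The aim needs one comparison, exercise versus no exercise among patients. Because section 2.8 goes by the number of groups, four subgroups lead to a one-way ANOVA with post-hoc pairs, while the abstract's wording suggests a pooled comparison of rehabilitation with control. These routes answer different questions and have different power for the same effect. If the choice stays open until the data are seen, a positive result could reflect disease status, or a real effect in patients could be diluted or missed.

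**Working it through.** **Inputs.** From section 2.7: difference 4 min, SD 3 min, alpha 5% (sidedness not stated, two-sided assumed), power 95%, 15 per subgroup, four subgroups. The patient–healthy difference in saccharin transport time, D, is not in the document. It is an assumption and is shown as a range.

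**1. The stated sample size.** For two groups, n = 2 × [SD × (1.960 + 1.645) / difference]² = 2 × [3 × 3.605 / 4]² = 14.62, rounded up to 15. Four subgroups of 15 give 60. The plan's figure is reproduced, as a two-group comparison of 15 with 15 and not as a four-group ANOVA.

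**2. Patient-only contrast, prespecified.** Noncentrality = 4 / (3 × √(2/15)) = 4 / 1.095 = 3.65. On 28 df, power is 94.1% (95.5% by the normal approximation).

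**3. The same contrast as one of six post-hoc pairs.** The noncentrality is again 3.65, now on 56 df with an adjusted critical value.
- Tukey, critical value 2.65: power 83.8%.
- Bonferroni, alpha 0.05/6, critical value 2.74: power 81.6%.

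**4. One-way ANOVA over four cells with no exercise effect.** Cell means are (D, D, 0, 0), so each lies D/2 from the grand mean. Then λ = 15 × 4 × (D/2)² / 9 = 15D²/9, on 3 and 56 df.

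| Assumed D (min) | λ | Probability that F is significant |
|---|---|---|
| 2 | 6.67 | 53% |
| 3 | 15.0 | 90% |
| 4 | 26.7 | 99% |

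**5. Exercise versus no exercise pooled over all 60.** Suppose the effect is 4 min in patients and 0 in healthy volunteers. The pooled effect is (4 + 0)/2 = 2 min.
- Residual SD 3 (disease and the interaction both in the model): noncentrality = 2 / (3 × √(2/30)) = 2.58, power 72%.
- No disease term, and D = 4 among non-exercisers: exercising patients then have the same mean as healthy volunteers, so the exercise arm keeps variance 9. The non-exercise arm has 9 + (4/2)² = 13. The average is 11. Noncentrality = 2 / √(11 × 2/30) = 2.34, power 63%.

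**6. Disease-by-exercise interaction of 4 min.** Its standard error is √(9 × 4/15) = 1.55, so noncentrality = 2.58 and power is 72%. Reaching 95% would take 30 per cell, 120 in total.

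**The case against.** Section 2.8 is a generic list of tests. It nowhere specifies an ANOVA over four cells; that follows only from combining it with the four subgroups of section 2.7. The t or Wilcoxon test applied to 15 versus 15 patients is exactly the contrast wanted, and the multiple comparisons step also contains that pair. The sample size calculation itself points to a two-group comparison. A separate analysis plan may name the contrast, and Figure 1, not shown here, may display the four cells.

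Most of this stands. A reader might infer that the planned analysis cannot isolate the effect of exercise in patients, but the document does not support that: the contrast is available and simply not fixed. A reader might also take the 53%, 90% and 99% as false-positive rates for exercise. They are not. In those scenarios the omnibus null is false, because patients and healthy volunteers do differ, and the figures mislead only if a significant F is read as an exercise effect.

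What does not stand is that the matter is only detail left to an analysis plan. Neither a figure nor an analysis plan makes sections 2.3, 2.5.1 and 2.5.2 agree on who exercises. The rule in section 2.8, applied to the four subgroups, leads to a route that falls short of the power stated in section 2.7.

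**Conclusion.** The point holds in this form: the group definitions contradict each other, and section 2.8 leaves unfixed the contrast that the aim and the sample size call for. For a 4-minute effect with SD 3, the route chosen moves power from about 94% (prespecified, patients only) to 84% or 82% (adjusted post-hoc pair), or to 72% or 63% (pooled, effect in patients only), against the stated 95%.

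The patient-only figures assume two-sided 5% tests, SD 3 and equal cells of 15. The pooled figures further assume no effect in healthy volunteers, and the 63% assumes a 4-minute disease difference among non-exercisers. The ANOVA rejection rates rest wholly on assumed disease differences. The contradiction between the sections depends on none of these.

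**What to change.** 1. Reconcile the abstract and sections 2.3, 2.5.1 and 2.5.2 into four named cells: bronchiectasis with exercise, bronchiectasis without, healthy with exercise, healthy without. State that disease status is observed and exercise is randomized, and use the term control group in one sense throughout.
2. In section 2.8, prespecify exercise versus no exercise within the 30 bronchiectasis participants as the single primary contrast. Estimate it directly, or from a model with disease, exercise and disease-by-exercise terms in place of the one-way ANOVA.
3. Make the interaction secondary, noting its power of about 72% for 4 minutes. Make the patient-versus-healthy comparison secondary too, and label it non-randomized.

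The cost is wording in the protocol and the analysis section. N stays at 60, because 15 versus 15 already gives the primary contrast about 94% power. It would need revisiting only if that contrast were tested as one of several adjusted pairs, or if the interaction became the primary question.

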## Introduction

1

Bronchiectasis is characterized by pathological and irreversible bronchial dilatation.^[1,2]^ It is mainly caused by inefficient removal of secretions and microorganisms, as well as the perpetuation of inflammatory processes induced by chronic or recurrent infections. The diagnosis is traditionally performed using high-resolution computed tomography (HRCT) in association with spirometry.^[3,4]^

Spirometry requires great cooperation from subjects. Alternative tests such as impulse oscillometry system (IOS) are suggested for patients who have difficulties in performing the forced manoeuvres.^[5]^ IOS evaluates the impedance of the respiratory system by applying oscillatory pressure waves at multiple frequencies. This technique has been shown to be more sensitive in the identification of airway alterations than spirometry.^[6,7]^ Clinically, the most frequent characteristic is an increase in the production of bronchial secretions. The mucus produced is thicker and results in slower transport, causing damage to the mucociliary transport.^[8]^ Patients may undergo exacerbation periods and acute deterioration of respiratory symptoms related to decreased quality of life, lung function, and increased mortality.^[4]^

The immune response in bronchiectasis is primarily mediated by neutrophils, and increased levels of chemokines and proinflammatory cytokines are found in the airways of affected individuals.^[8]^ High levels of proteases are present at inflammation sites, resulting in the release of proinflammatory cytokines. This causes even more damage to the cells of airway structures.^[9]^ In approximately 50% of cases, there is a diagnosis of a primary disease causing bronchiectasis.^[10]^ Thus, a single clinical or functional parameter is insufficient to assess the severity of the disease. In an attempt to elucidate this problem, Chalmers et al^[11]^ developed the Bronchiectasis Severity Index and concluded that it more accurately stratifies mortality risk, hospital admissions, and future risk of exacerbations. Patients may benefit from specific physiotherapy techniques for the removal of secretions from the respiratory system, as well as overall exercises within pulmonary rehabilitation programs.^[12]^ However, there is little information on the effects of physical training in patients with bronchiectasis.

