Regular physical training can modify the autonomic balance and may accelerate the physiological recovery of the vagal sympathetic interaction.^[56]^ The autonomic nervous system acts on mucociliary clearance. Patients subjected to lung transplantation present a reduction in mucociliary clearance due to denervation since the vagus nerve mediates the main components of the mucociliary clearance system, the frequency of ciliary beats, and mucus secretion.^[57,58]^

The present study could provide new information about the unclear mechanisms regarding exercise to aid in the removal of secretions. We expect to identify whether mucociliary transport dysfunctions occur through only the oscillations promoted by increased airflow and body movement during exercise, or whether there are other mechanisms related to pulmonary mechanics, inflammation, or the autonomic nervous system.

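### The only association analysis is an unadjusted correlation in a sample that mixes cohorts and exercise groups, so a significant result may reflect group membership

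*Protocol article*

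**What the plan says.** Section 2.8 (Statistical analysis) compares groups with t, Wilcoxon, analysis-of-variance and Kruskal–Wallis tests. Its only provision for relating two measurements is: "Data correlation will be assessed using the Pearson or Spearman correlation test for normal and nonnormal distributions, respectively". The choice between the two tests depends on normality. No adjustment or stratification is mentioned.

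The Abstract describes the sample as "30 volunteers with clinically stable bronchiectasis and 30 healthy volunteers". Section 2.4 adds: "The remaining participants will be 30 nonsmoker volunteers without lung disease and recruited from the community". Section 2.3 divides participants by exercise, and section 2.7 arrives at four subgroups of 15. I read these as patient or healthy, crossed with exercise or none. Assessments are at the start and after weeks 8 and 12.

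On what distinguishes patients, the Introduction says of transport: "The mucus produced is thicker and results in slower transport, causing damage to the mucociliary transport". On inflammation it says that "increased levels of chemokines and proinflammatory cytokines are found in the airways of affected individuals", and it goes on to describe dysautonomia in bronchiectasis. The Discussion says the study expects to show whether the transport dysfunction works only through airflow and body movement "or whether there are other mechanisms related to pulmonary mechanics, inflammation, or the autonomic nervous system".

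**The concern.** The question in the Discussion is about association: does transport move with mechanics, inflammation or autonomic function? Of the methods in section 2.8, only the correlation test relates two such measurements. In a sample built from groups that differ, an unadjusted correlation combines two things: how the variables move together within a group, and how far apart the group means lie. Only the first bears on mechanism.

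The protocol itself gives reason to expect the second. It describes patients as having slower transport, raised airway cytokines and probable autonomic disturbance. After baseline, an exercise effect on two variables would do the same between arms, even if the two responses were unrelated within persons. A significant coefficient could then be taken as support for a mechanism when it shows only that the groups differ on both measures.

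**Working it through.** **The plan's own scale.** Section 2.7 states: "The detected effect should have an average of 4 minutes with a standard deviation of 3 minutes, alpha of 5%, and power of 95" per cent. By the two-sided normal approximation, n per group = 2 × (1.960 + 1.645)² × 3² / 4² = 2 × 12.996 × 0.5625 = 14.6, so 15. Four subgroups give 60, as stated. The standardised effect is 4/3 = 1.33 SD. The section does not say which contrast the 4 minutes describes, so using 1.33 SD below as a cohort shift or as an arm shift is an assumption.

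**Inputs.**
- From the documents: 30 patients and 30 healthy volunteers; 15 per subgroup; 5% significance level (taken as two-sided).
- Assumed: shifts of 0 to 1.33 SD between groups on each variable, normal data, and zero correlation within every group. The documents give directions of difference but no sizes.

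**Correlation created by mixing.** For two equal groups with unit within-group SD, zero within-group correlation and mean shifts d1 and d2:

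r = (d1·d2/4) / √[(1 + d1²/4)(1 + d2²/4)]

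- d1 = d2 = 0.5: 0.0625/1.0625 = 0.06
- d1 = d2 = 1: 0.25/1.25 = 0.20
- d1 = d2 = 1.33: 0.444/1.444 = 0.31
- either shift zero: r = 0

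The two-sided 5% critical value of |r| is t/√(n − 2 + t²). For n = 60 it is 2.002/√(58 + 4.007) = 0.254. For n = 30 it is 2.048/√(28 + 4.196) = 0.361.

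**Cohorts pooled, 30 + 30** (10,000 simulated trials per row):

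| Shift on the two variables (SD) | Pearson rejects | Spearman rejects | Cohort-adjusted partial rejects |
|---|---|---|---|
| 1.33 and 0 | 5.5% | 5.2% | 5.2% |
| 0.5 and 0.5 | 7.1% | 7.1% | 4.9% |
| 0.8 and 0.8 | 18.6% | 18.2% | 4.9% |
| 1 and 1 | 34% | 35% | 5.2% |
| 1.33 and 0.8 | 37% | 37% | 5.5% |
| 1.33 and 1.33 | 70% | 73% | 5.0% |

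Choosing Spearman when normality fails gives no protection.

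**Patients only, after baseline, two arms of 15** (20,000 trials; 1.33 SD on saccharin time). The unadjusted Pearson test rejects in 11%, 20%, 27% and 40% of trials when the marker shifts by 0.5, 0.8, 1 and 1.33 SD. Adjusted for arm, it rejects in about 5% throughout.

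**All 60 after baseline, exercise acting in patients only** (1.33 SD on saccharin time, 0.8 SD on the marker; 20,000 trials). Adjusting for cohort alone leaves 14.5%. Cohort plus exercise group leaves 7.5%. Adjusting for all four subgroups gives 5.2%.

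**The case against.** The strongest reply is that pooling is inferred. The sentence in section 2.8 names no variables, visit or analysis set, and a patients-only or within-cohort correlation fits it just as well. This is also a journal article, and such details may sit in a fuller document. That stands: a reader might infer that the protocol correlates across both cohorts and will therefore reject because of disease status, but the text does not say so. The point rests on the method that is stated, not on missing detail. A patients-only reading also removes only the cohort problem, since post-baseline patient data still mix the two arms.

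Second, a pooled correlation is a valid test of marginal association, so rejecting when a marginal association exists is not a type I error in the strict sense. That also stands. The percentages count rejections when there is no within-group link. The fault is confounded interpretation, not a broken reference distribution.

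Third, expected differences on both variables are only partly documented. Autonomic disturbance is called probable and poorly studied, no oscillometry difference is stated, and the cytokine assay in section 2.6.1.6 is on nasal lavage although the Introduction speaks of the airways. This limits the size of the problem for particular markers. It does not remove it: section 2.6.1.4 also stores breath condensate for cytokine levels and presents it as informative about the lower airways.

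Fourth, section 2.8 does not tie the correlation to the mechanism question, to a listed outcome or to the sample size. The group comparisons of the effect of exercise are indeed untouched.

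**Conclusion.** The concern holds conditionally. The stated method cannot separate a mechanism–transport link from group membership if cohorts are pooled or arms are mixed after baseline. Under assumed shifts and no within-group association, rejection at nominal 5% runs from about 7% to about 70% for pooled cohorts and from 11% to 40% for patients with arms mixed. It stays near 5% if only one of the two variables differs between groups, and a correlation at baseline within one cohort is unaffected.

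No rate in this range can be called the trial's actual rate, because the documents give no cohort difference, do not identify the contrast behind the 4 minutes and do not state that cohorts are pooled. What is at stake is the mechanistic reading in the Discussion. The change is worth making because it is cheap and works whichever analysis set was intended.

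**What to change.** Replace the correlation sentence in section 2.8 with wording such as: *Associations will be estimated as partial (Pearson or rank) correlations with 95% confidence intervals, adjusted for cohort whenever healthy volunteers are included and for allocated exercise group whenever post-baseline data are used.* Where both apply, adjusting for the four subgroups is safer, because exercise may act differently in patients and in healthy volunteers.

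No new data are needed and the code is trivial. The adjustment costs one or two degrees of freedom, or three with the four subgroups. Restricting the analysis to patients, or to changes from baseline to week 12, is optional and has a price. At a within-cohort correlation of 0.3, power is about 65% with all 60 participants and cohort adjustment, against 37% in 30 patients. At 0.5 it is about 98% against 82%.
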